### Standardisation of speech pathologists performing CFE + CA

Prior to the commencement of the study, all speech pathologists involved in the assessment of participants will be asked to read through and familiarise themselves with a folder containing a (1) swallowing sound definition sheet; (2) a compact disc (CD) of ten audio examples of normal swallows of puree, lumpy mash, biscuit (chewable) and thin fluids (bottle and cup) in children and one adult; (3) a sheet containing website links to respiratory sound examples of wheeze, stridor, crackles and normal breathing in children; (4) the data collection form. This training package was provided to help attune the clinician’s perception of swallowing sounds and definitions prior to their involvement in the study. The swallowing sounds definition sheet is in Additional file 1.

### Inter-rater reliability

Inter-rater reliability for the detection of OPA will be determined on 20 swallowing sounds scored independently by four speech pathologists who have familarised themselves with the training package, as outlined above. Intra-rater reliability will also be determined for these same 20 sounds. Three swallowing sound clips of swallows from healthy children (with no oropharyngeal aspiration/penetration), four sound clips of abnormal swallows (from patients with radiologically defined oropharyngeal aspiration) and three sound clips of abnormal swallows (from patients with radiologically defined penetration) will be recorded onto a CD twice in random order based on a computer-generated randomisation list, giving a total of 20 examples.

Good to very good intra-rater reliability kappa scores [36] will be accepted for continued involvement in the study. Speech pathologists who do not meet this criterion will receive specific training with the researcher to discuss perceptual characteristics of normal and OPA identified swallows, as confirmed on MBS.

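### The intra-rater kappa that decides whether a speech pathologist needs further training comes from 10 clips repeated within one shuffled 20-item list, so recall of earlier answers can inflate it

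*Protocol article*

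**What the plan says.** The section 'Inter-rater reliability' of the Protocol article builds the test from three sets of clips. The first is "Three swallowing sound clips of swallows from healthy children". The second is "four sound clips of abnormal swallows (from patients with radiologically defined oropharyngeal aspiration"). The last set is "three sound clips of abnormal swallows (from patients with radiologically defined penetration"). All of these clips "will be recorded onto a CD twice in random order based on a computer-generated randomisation list, giving a total of 20 examples". The items are "scored independently by four speech pathologists".

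The same material serves for repeatability: "Intra-rater reliability will also be determined for these same 20 sounds". The result has a consequence: "Good to very good intra-rater reliability kappa scores [36] will be accepted for continued involvement in the study". For the others, "Speech pathologists who do not meet this criterion will receive specific training with the researcher", using sounds confirmed on MBS. No re-test after that training is described.

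The section gives no interval, second sitting or minimum spacing between the two copies of a clip. The Discussion adds that inter- and intra-rater reliability will also be assessed while the study runs, again without an interval.

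**The concern.** Intra-rater kappa should show whether a clinician who hears the same sound afresh gives the same answer. When both hearings sit in one short shuffled list, the second answer may be a fresh judgement or a memory of the first, and the kappa cannot tell them apart. Recall can only push agreement up.

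The kappa is also used as a threshold, which makes this more than a matter of reporting. A speech pathologist whose judgements are not repeatable, but who recognises some clips, can clear it and so miss the MBS-based training. The Discussion names clinician variability as a limitation and offers the reliability work as part of the answer. An inflated kappa weakens that assurance.

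**Working it through.** **Inputs from the protocol.** 3 + 4 + 3 = 10 distinct clips; 10 × 2 = 20 items, which reproduces the stated total. Each rater therefore supplies 10 test-retest pairs.

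**Assumptions.** The CD is heard as one continuous list. The section prints no numeric cut-off for a good kappa, so I take 0.60 and show both at least 0.60 and strictly above it. The recall shares of 0, 30% and 50% are illustrative; the document gives none.

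**Spacing, one full shuffle of 20.** For a given clip, P(gap = d) = (20 − d)/190.
- P(gap ≤ 3) = (19 + 18 + 17)/190 = 54/190 = 28%.
- The cumulative count is 85/190 = 45% at d = 5 and 99/190 = 52% at d = 6, so the median gap is 6. The mean is 7.
- P(gap = 1) = 19/190 = 10%, so one of the 10 pairs on average is back to back. By inclusion-exclusion, 64% of lists contain at least one such pair.

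**Spacing, two shuffled blocks of 10.** This is the more favourable layout that the wording could also cover. P(gap = d) = (10 − |d − 10|)/100. The median is 10, P(gap ≤ 3) = (1 + 2 + 3)/100 = 6%, and a back-to-back repeat occurs in 10% of lists.

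**Effect of recall on kappa.** Suppose the second answer equals the first with probability k and is otherwise an independent draw, so that true kappa is k. If a share r of repeats is simply remembered, the expected agreement corresponds to k′ = k + r(1 − k).
- k = 0.4: k′ = 0.4 + 0.3 × 0.6 = 0.58 at 30% recall, and 0.4 + 0.5 × 0.6 = 0.70 at 50%.
- k = 0.2: k′ = 0.2 + 0.3 × 0.8 = 0.44 at 30% recall, and 0.2 + 0.5 × 0.8 = 0.60 at 50%.

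**Chance of passing.** I enumerated all outcomes of 10 pairs exactly, with the rate of positive answers between 0.4 and 0.7:

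| True kappa | Recall | Pass, kappa ≥ 0.60 | Pass, kappa > 0.60 |
|---|---|---|---|
| 0.4 | 0 | 26-27% | 18-23% |
| 0.4 | 30% | 49% | 39-44% |
| 0.4 | 50% | 66-68% | 58-62% |
| 0.2 | 0 | 10-11% | 6-9% |
| 0.2 | 30% | 30-31% | 22-27% |
| 0.2 | 50% | 51-52% | 42-46% |

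The two columns differ because 8 agreements in 10 with even margins give (0.8 − 0.5)/(1 − 0.5) = 0.60 exactly.

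**Precision, apart from recall.** At that same result the standard error is √(0.8 × 0.2/10)/0.5 = 0.25, so an approximate 95% interval is 0.60 ± 0.50. With no recall, a rater with true kappa 0.8 still fails 17-20% of the time at the ≥ 0.60 rule and 23-24% at the strict rule.

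**The case against.** The strongest reply is that the protocol never says the CD is heard in one sitting, and that a journal article may leave session timing to the full protocol. It is right that one sitting is the plain reading and not a stated fact. But the layout itself is stated: two copies of every clip in a single random order. Splitting that list over two sittings would not separate the copies unless it were split by copy, and no second scoring occasion is described. If the order were two shuffled blocks of 10, close repeats would be far fewer, but the copies would still be only about 10 items apart.

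Second, the size of the recall effect is assumed. That stands. The document gives no clip length, says nothing on how distinctive the clips are, and does not say whether raters know that clips repeat. With no recall there is no inflation.

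Third, a reader might infer that unrepeatable listeners do reach the threshold. The figures do not support that. Even with 30% recall, a rater with true kappa 0.2 fails about 70% of the time. A rater who guesses at random passes 28-38% of the time at 50% recall and 58-68% at 70%, so would need roughly 60-70% recall to pass more often than not.

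Fourth, a reader might infer that the CFE + CA versus CFE comparison is biased towards no difference. The documents do not establish this. Failing the criterion leads to training, not to stated exclusion. Repeatability is not accuracy. The decision in the CFE + CA group also draws on clinical signs and on all observed swallows of a consistency, not on one isolated clip.

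**Conclusion.** The point holds as a weakness in a stated test layout. The kappa used to decide who continues without further training can be inflated by recall, because nothing separates the two hearings of a clip. Under the plain reading, more than a quarter of repeats fall within three items of the first hearing. With a pass at 0.60 or above, 50% recall would raise the pass rate of a rater with true kappa 0.4 from about 26% to about 67%. That size rests on the assumed cut-off, the assumed recall shares and a single continuous list.

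The harm is confined to the rater check and to the reliability figure reported from it. Any effect on the trial's main comparison would be indirect and has not been calculated. This is an inexpensive improvement, not a fault that threatens the trial.

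**What to change.** Put each of the 10 clips once on each of two lists with separate random orders. Have each speech pathologist score the second list in a separate sitting at least 1-2 weeks after the first, without access to the first answers. Calculate intra-rater kappa across the two sittings and report it with its 95% CI. Recruitment began in October 2012, so the first rater test may already be complete; the same layout should then be used for the reliability checks that the Discussion plans during the study.

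The cost is one further short listening session per speech pathologist, with the same clips and no extra staff or patients. The change does not cure the imprecision of 10 pairs: chance passes by weak raters and chance failures by good ones remain, and the confidence interval will make this visible.

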### Procedure and equipment

#### Clinical feeding examination with cervical auscultation (CFE + CA)

Standardised procedures and data collection will be undertaken. Children may be fed by their caregiver, treating speech pathologist or nurse, depending on the child’s preference and/or medical needs.

Swallowing sounds are recorded using an omnidirectional condenser microphone with sensitivity at 1 kHz of 10 mV/Pa, impedance 200 and frequency range 20 to 20,000 Hz (Model C417, AKG Acoustics, Vienna, Austria) [37]. The microphone is attached (by tape) on the lateral border of trachea, immediately inferior to the cricoid cartilage, by the principal researcher only for consistency. Recordings of swallow sounds will be digitally recorded (Digital H4n Handy Recorder, Zoom Corp., Tokyo, Japan). Nasal airflow direction will be measured by an infant- or paediatric-sized cannula placed at the entrance of each nostril and secured firmly behind the ears [34,38]. The quality of sound is monitored consistently throughout the session by listening to extraneous noises (e.g. carotid artery, room noises, reduction of skin-to-skin contact). The researcher or clinician monitors the sound quality and adjustments are made where necessary. To confirm the onset of a swallow, a digital video recorder (model DCR-DVD605E, Sony Corp., Tokyo, Japan) will be used to provide visuals of laryngeal movement associated with the swallow. Nasal airflow data and visuals of the child’s performance will be simultaneously recorded onto the Digital Swallowing Workstation (KayPENTAX, PENTAX Medical Co., NJ, USA). A vocal signal will be used at the beginning of all assessments so synchronisation of acoustic, nasal airflow and visual data can be undertaken. The treating speech pathologist will wear headphones (Model ATH-M50, Audio-Technica, Taiwan) to access the recorded swallowing sounds during the assessment.

Children will be offered three bites or sips/mouthfuls of each age-appropriate food/fluid item (Table 1) followed by free eating/drinking to finish the test meal [39,40].

**Table 1 T1:** **Standard presentation of food and fluids during CFE, CFE** + **CA or MBS**

**Age**	**Food and fluid**
4 – 6 months	● Puree
	● Thin fluids via breast or bottle feeding
8 – 12 months	● Puree
	● Lumpy mash
	● Thin fluids via breast, bottle or spout cup
1 – 18 years	● Puree
	● Lumpy mash
	● Chewable solids (biscuit)
	● Thin fluids via breast, bottle or open cup

Three bites or sips of food or fluid are consistent with normative data obtained previously in adults [41,42] and allow for variations in normal swallowing [32,43]. However, the protocol can be modified at the discretion of the speech pathologist depending on the presentation of the child’s observed feeding and swallowing skills. Reasons for potential protocol modification include:

● Suspected OPA on thin fluids, requiring presentation of thickened fluids prior to thin fluids

● Significantly delayed chewing skills, requiring elimination of an age-appropriate solid consistency

● Reduced compliance from the child, requiring early termination of the session

#### Clinical Feeding Examination (CFE)

The procedure for CFE is similar to the CFE + CA process; however, the treating speech pathologist will not wear the headphones to access the recorded swallowing sounds during the assessment.

#### Modified Barium Swallow (MBS)

After the clinical evaluation (CFE + CA or CFE), all children will undergo an MBS to objectively define the presence or absence of OPA. The MBS will occur within 2 weeks following the CFE, pending clinical constraints.

During the MBS, swallowing sounds and video recording will be undertaken using the same procedure described above. The MBS will be simultaneously recorded onto a Digital Swallowing Workstation (KayPENTAX, PENTAX Medical Co., USA). A vocal signal will occur at the beginning of all procedures for ease of later synchronising of acoustic and exam data. Our standard clinical protocol is adapted from previous research protocol recommendations for paediatric MBS [3,5,24,44,45].

The presence and severity of OPA will be determined using the Penetration-Aspiration Scale (PAS) [23,46,47]. The PAS describes the severity of penetration of radiology contrast into the airway and the airway response to the penetration using an ordinal 1 to 8 scale, where 1 = no aspiration and 8 = silent aspiration. This scale has high inter- and intra-rater reliability for determining the severity rating of OPA [15,21,23]. PAS scores will be determined for each food and fluid consistency trialed in the MBS. A score of 6, 7 or 8 will be classified as OPA present, while scores of 1, 2, 3, 4 and 5 will be classified as OPA absent.

### Data collection

#### Clinical signs of OPA (both groups)

All speech pathologists will adhere to Speech Pathology Australia’s Dysphagia Clinical Guidelines when completing the CFE [48]. CFE parameters of coughing, gagging, voice changes, colour changes, delayed swallow, abnormal laryngeal elevation, oxygen desaturation, eye tearing and wet breathing have been associated with oropharyngeal aspiration when a combination of any of the above are observed during the clinical feeding examination [5,12-14,35,49-53]. In particular, cough is the most significant and consistent clinical sign suggestive of OPA [5,12]. Multiple swallows and laboured breathing have been included as clinical signs suggestive of increased risk of OPA. We have also included: snuffly nose, rattly chest and fremitus as clinical signs of OPA that have been previously observed in clinical practice.

#### Perceptual parameters (CFE + CA group only)

Perceptual parameters for sounds heard throughout the pre-swallow, swallow and post-swallow phases are listed in Table 2.

**Table 2 T2:** **Pre-swallow, swallow and post-swallow sound parameters used in CFE** + **CA**

**Pre-swallow**	**Swallow**	**Post-swallow**
Normal breathing [54]	Crisp and clear ‘distinct’ [56]	Normal breathing [54]
Wet breathing [5,54]	Quick [54]	Wet breathing [5,54]
Rattly chest	Loud	Rattly chest
Grunting	Initial discrete sound (IDS) [32,55,57]	Grunting
Crackles	Bolus transit sound (BTS) [32,55,57]	Crackles
Stridor	Final discrete sound (FDS) [32,57]	Stridor
Wheeze	Glottal release sound (GRS) [55]	Wheeze
Throat clearing	Coordinated	Throat clearing
Coughing [12-14]	Uncoordinated	Coughing [12-14]

Pre- and post-swallow sounds are predominantly respiratory sounds that have been heard in association with aspiration pneumonia. The parameter ‘normal breathing’ is based on Rommel and colleagues’ [54] study of swallowing sounds in children, while ‘wet breathing’ is obtained from Weir and colleagues’ [5] findings of a statistically significant correlation between OPA and the clinical feature of ‘wet breathing’. Coughing and throat clearing were included as cough has been associated with OPA [12-14]. Swallow sounds were based on features previously described in the normal swallows of adults [32,55,56] and infants [54,57].

#### Outcome measures

PAS [23,46,47] scores will be used to objectively determine presence or absence of OPA on MBS, with a score of 6–8 indicating OPA. For CFE, one or more ticked clinical signs of OPA (cough, gagging, voice changes, colour changes, unable to initiate swallow, abnormal laryngeal elevation, oxygen desaturation, eye tearing, multiple swallows, choking, wet breathing, laboured breathing, fremitus, snuffly nose/stertor) [5,12-14,35,49-53] and clinician decision (yes/no) for suspected OPA. For CFE + CA, evaluation was as for CFE outcome measurements and clinician decision (yes/no) for suspected OPA based on pre-, during and post-swallow sound parameters, as listed in Table 2. Presence or absence of OPA is determined by the clinician across all observed swallows for each given texture/consistency in the CFE and MBS. Presence of OPA need only occur once for a child to be marked positive for OPA on that consistency/texture.

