### Statistical analyses

Baseline characteristics of the two groups will be presented as means/medians or proportions and their 95% confidence intervals and compared using *t*-tests for normally distributed data, using chi-square tests for proportions and the appropriate non-parametric methods for non-normally distributed data. Baseline demographic and clinical characteristics for those who do and do not withdraw will also be completed. A secondary analysis to re-present the primary results for each of the strata (<1 year and >1 year) will be done to account for the stratification.

For our primary aim, agreement between OPA determined clinical and MBS assessments will be calculated using percent agreement and a kappa coefficient. All evaluable data will be used minus the 8% of dropouts. Taking MBS determination of presence or absence of OPA as the gold standard, sensitivity, specificity, negative predictor value (NPV), positive predictor value (PPV), pretest probability and likelihood ratios will also be calculated. Likelihood ratios will also be calculated.

For our secondary aim, categorical variables of pre-, during and post-swallowing sound parameters will be analysed using a chi-square test to determine which sound qualities are significantly associated with OPA. Multivariate regression analysis will be used to determine whether age, gender, texture, method of intake or clinician level of experience are independent predictors associated with the absence/presence of OPA. All variables will be analysed univariably, then include all those with *p* < 0.15 in a multivariable model. Forward stepwise regression modelling will be employed to identify variables independently associated with OPA and account for interaction effects. The *a priori* statistical level of significance is *p* < 0.05. Missing data points will be coded as a number on the database and analysis completed on the remaining data.

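### OPA is defined per texture, not per child: the unit of the primary accuracy analysis is not fixed, and the secondary texture-level tests make no allowance for several correlated results per child

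*Protocol article*

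**What the plan says.** All references are to the protocol article.

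- **Modified Barium Swallow (MBS):** "PAS scores will be determined for each food and fluid consistency trialed in the MBS". Scores of 6 to 8 count as OPA present.
- **Outcome measures:** presence or absence of OPA "is determined by the clinician across all observed swallows for each given texture/consistency in the CFE and MBS". The rule for a positive result is "Presence of OPA need only occur once for a child to be marked positive for OPA on that consistency/texture". It combines swallows within a texture and stops there.
- **Table 1:** two items at 4–6 months, three at 8–12 months and four at 1–18 years. The text below the table lets the speech pathologist change the set, for instance by dropping a solid, or when suspected OPA leads to "requiring presentation of thickened fluids prior to thin fluids". A child can therefore have fewer or more results than the table shows.
- **Sample size:** 108 children per group, for 80% power to detect a 15-point difference from 76%.
- **Statistical analyses, primary aim:** percent agreement, kappa, sensitivity, specificity, predictive values and likelihood ratios. The unit is not stated.
- **Statistical analyses, secondary aim:** the sound parameters "will be analysed using a chi-square test to determine which sound qualities are significantly associated with OPA". In addition, "Multivariate regression analysis will be used to determine whether age, gender, texture, method of intake or clinician level of experience are independent predictors" of OPA, with univariable screening at p < 0.15 and forward stepwise selection.

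**The concern.** The outcome definition and the sample size use different units. The outcome exists only per child and texture, while the sample size counts children with one result each. Two consequences follow.

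**Primary aim.** An analyst could use one result per child, one texture at a time, or all texture rows pooled, and these answer different questions. Take a child judged positive clinically on puree only and positive on MBS on thin fluid only. Under an any-texture rule the child is one true positive. Texture by texture, the same child gives one false positive and one false negative. If the unit is chosen after the data are seen, the choice can move the main result.

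**Secondary aim.** Texture varies within a child, so a regression with texture as a predictor needs several rows per child. Those rows share the child's anatomy, age and swallowing function, so they are likely to be correlated. A chi-square test, or a regression that ignores this, gives wrong standard errors. They are too small for factors that are constant within a child (age, gender) and possibly too large for factors that vary within a child (texture). Stepwise selection then carries the error into the choice of predictors.

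**Working it through.** **1. The plan's own figure.** Inputs from Sample size: p1 = 0.76, p2 = 0.76 + 0.15 = 0.91, two-sided α = 0.05, power 0.80. With mean proportion 0.835:

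n₀ = [1.96·√(2·0.835·0.165) + 0.842·√(0.76·0.24 + 0.91·0.09)]² / 0.15² = 94.9, or 95 without continuity correction.

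n = (n₀/4)·[1 + √(1 + 4/(n₀·0.15))]² = 107.9, or **108 per group**.

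This matches the stated 108. The formula assumes one independent binary result per child.

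**2. Assumptions.** The document gives no within-child correlation. I assume an ICC of 0.2 to 0.5. The number of textures m (2, 3 or 4) comes from Table 1.

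**3. Child-level factors (age, gender) tested on texture rows.** Design effect DE = 1 + (m − 1)·ICC. True type I error of a nominal 5% test = 2·[1 − Φ(1.96/√DE)].

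| m | ICC | DE | True type I error |
|---|---|---|---|
| 2 | 0.2 | 1.2 | 7.4% |
| 2 | 0.5 | 1.5 | 11.0% |
| 3 | 0.3 | 1.6 | 12.1% |
| 4 | 0.3 | 1.9 | 15.5% |
| 4 | 0.5 | 2.5 | 21.5% |

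**4. Sound parameter against OPA.** Sound parameters are recorded in the CFE + CA group only, and they can differ between a child's textures, so step 3 does not apply. If both variables have the same ICC, the approximate design effect is 1 + (m − 1)·ICC². The simulation used 108 children, prevalence 0.3 for each variable (assumed), no true association and 4,000 runs per setting.

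| m | ICC | DE | Formula | Simulated |
|---|---|---|---|---|
| 3 | 0.2 | 1.08 | 5.9% | 5.3% |
| 3 | 0.3 | 1.18 | 7.1% | 7.7% |
| 3 | 0.5 | 1.50 | 11.0% | 11.6% |
| 4 | 0.2 | 1.12 | 6.4% | 6.2% |
| 4 | 0.3 | 1.27 | 8.2% | 7.8% |
| 4 | 0.5 | 1.75 | 13.8% | 14.3% |

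With ICC = 0 the simulated rate was 5.2% to 5.3%, as it should be.

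**5. Primary measures, by choice of unit.**

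- One result per child, or one texture at a time: DE = 1, and the intervals are not affected.
- All rows pooled, percent agreement: DE is 1.2 to 2.5 as in step 3. The naive interval is too narrow by 1 − 1/√DE, that is 9% to 37%. At m = 4 and ICC 0.5, 4 × 108 = 432 rows carry the information of 432/2.5 ≈ 173.
- All rows pooled, sensitivity: only MBS-positive rows enter, so the clusters are smaller. With texture-level prevalence p = 0.3 (assumed) and the same ICC for both results, DE = 1 + ICC·(m − 1)·[p + ICC·(1 − p)]. For m = 4 this gives 1.26, 1.46 and 1.98 at ICC 0.2, 0.3 and 0.5. These are below the 1.6, 1.9 and 2.5 of the simple formula.

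**The case against.** The strongest case on the other side has four parts.

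1. **The primary outcome reads as one per child.** The abstract speaks of a single presence or absence of OPA, and the sample size counts children. Reporting by texture is also plausible, because the Background gives separate CFE sensitivities for fluids (92%) and solids (33%). Under either reading each child gives one record per estimate. This stands. A reader might infer that the planned intervals for sensitivity, specificity and kappa are wrong, but the article nowhere says that texture rows will be pooled. What remains is that two readings are open and neither is fixed.

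2. **The regression is not called ordinary.** The article names no variance estimator, and a SAP that is not shown might add one. This stands in part. Silence on software detail would be no finding. But the section names the chi-square test, the screening threshold and the selection method, and a chi-square test on several rows per child is invalid as stated. For those tests the multi-row structure is the natural reading; for the regression it is unavoidable.

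3. **The 7–22% is not the error rate of every test.** A reader might apply it to the comparison of the two arms or to the sound-parameter tests. Neither is supported. The article names no between-arm test on texture rows, and arm is not among the listed predictors. For the sound parameters the figure is about 5–14%.

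4. **Older children, with more items, would outweigh infants if rows were pooled.** The planned re-presentation of primary results by age stratum deals with part of this.

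**Conclusion.** The concern holds in this form. OPA is defined only per texture, no rule gives the one result per child that the sample size assumes, and the secondary-aim methods as stated ignore within-child correlation.

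For an assumed ICC of 0.2 to 0.5, type I error at a nominal 5% is about 5–14% for the sound-parameter chi-square with 3–4 textures and about 7–22% for child-level factors with 2–4 textures. The size rests on that ICC, on the same number of textures for every child within a setting and, for the chi-square simulation, on prevalences of 0.3. The direction for child-level factors does not depend on these values as long as the correlation is positive. For within-child terms such as texture, the standard errors may instead be too large.

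For the primary measures the defect is an unfixed unit, not intervals shown to be wrong. The certain clustering problem lies in a secondary aim, and the remedy changes neither data collection nor sample size. It should be fixed, but it does not undermine the design.

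**What to change.** **Outcome measures.** Make the child the unit of the primary accuracy analysis, to match the sample size. State one rule that turns texture results into a child-level result, and apply it identically to the clinical assessment and the MBS, using only textures tested in both. Positive on any such texture is one defensible rule. Because it counts the puree/thin-fluid mismatch as a true positive, report accuracy with clinical and MBS results paired on the same texture as a supportive analysis.

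**Statistical analyses.** State the unit for each measure. For texture-level data, replace the chi-square tests and the regression with GEE or mixed logistic models, or use cluster-robust or cluster-bootstrap variance, with the child as cluster. Use the same approach for intervals on any accuracy estimate that pools textures.

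**Cost.** Wording and standard software. Most texture-level intervals become wider. The figure of 108 per group is unaffected by this change.
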